### Description of School Nutrition Programme intervention

The SNP aimed to prevent malnutrition among primary school children. The rationale of SNP was to increase the children’s nutrition and physical activity knowledge, attitude and practices to optimise their healthy lifestyle by encouraging them to eat healthily and stay physically active. The SNP is based on the Social Cognitive Theory (SCT) [29], which emphasises the importance of social and environmental factors in determining the psychosocial and behavioural risk factors of both undernutrition and overnutrition. The SNP is composed of two main components: (1) delivering nutrition education through School Nutrition Campaign for 3 months; and (2) serving healthy menu during school recess time to the children over a period of 3 months. The children of the intervention group participated in three School Nutrition Campaigns, in addition to the standard Physical dan Health Curriculum. The children in the comparison group received standard Physical and Health Curriculum and school canteen food handler were reminded to follow canteen guidelines by MOE Malaysia.

For nutrition education component, the researchers conducted three School Nutrition Campaigns using the three different nutrition education modules and education materials of Healthy Kids Programme [30]. These nutrition education modules included four main aspects, namely health awareness, nutrition, physical activity and hygiene. Specifically, module 1 comprised six topics with the goal of educating primary school children on the importance of healthy lifestyle and introduce the concept of food pyramid, physical activity and personal hygiene. Module 2 comprised six topics with the goal to provide more in-depth knowledge on food groups in the Malaysian Food Pyramid and Physical Activity Pyramid. Module 3 comprised five topics with the goal to strengthen the important skills to apply the knowledge that the children learnt from module 1 and module 2. These modules incorporated the “fun while learning” concept, with various attractive engagement activities such as act and guess, role-play, quiz and detective games. There was a four-week gap between each campaign, with at least 6 hours per campaign.

The training of trainers (TOT) aimed to provide hands-on training to the teachers to carry out the nutrition education component of the SNP, and to empower them to convey healthy lifestyle messages to the children during the School Nutrition Campaigns. As there were three modules, three separate sessions of the TOTs (1 day training session for each TOT) were needed to be completed by the teachers. The trained teachers conducted the nutrition education sessions to the children during the School Nutrition Campaigns and each topic took approximately 1 hour to deliver.

The second component of the SNP is a supportive healthy school food environment, which aimed to increase the availability of healthy foods in primary school canteen and to provide training to the canteen food handlers. A 1-day TOT of canteen food handlers was conducted to all food handlers by using a revised Healthy Catering Module from the Nutrition Division, MOH Malaysia [31], with incorporation of a few interactive games during the training. The food handlers learned to serve healthier foods, the fundamentals of preparing healthy foods, recipe modification, menu planning and healthy cooking techniques. All canteen food handlers needed to fulfil the basic requirements from the MOE Malaysia, which were to attend the Food Handling Course and compulsory get anti-typhoid vaccination [32].

During the TOT of canteen food handlers, the canteen food handlers discussed and planned a one-month healthy menu together with the researchers. One-week after the TOT of canteen food handlers, all canteen food handlers prepared four menus assigned by the researchers during Menu Testing Day. Stakeholders (such as principal, student affair teacher, Parent Teacher Association and school children) were invited to taste the healthy menu. Their comments and feedbacks were noted and used to further improve the menu. The healthy menu should contain a variety of food groups, such as from rice, noodle or bread, vegetable, fruit, and meat or chicken. Local food availability and children’s acceptability were taken into consideration when planning for the healthy menu. All menus were monitored by researchers and the trained teachers during the intervention period. Therefore, students would be able to practise healthy eating during school recess. Throughout the study period, the researchers would inform and remind the children about the importance of programme adherence.

### Measurements

All participants in both intervention and comparison groups were assessed prior to the start of the programme (Pre-Intervention), one-week right after completing the School Nutrition Campaigns (Post-Intervention I) and three-month afterwards without intervention (Post-Intervention II). The questionnaires were prepared in Malay, Chinese and Tamil languages to ease the children in understanding the questionnaires better. The anthropometric measurements and cognitive assessments of the children were conducted by trained researchers.

#### Socio-demographic background

In the present study, socio-demographic background of children in both intervention and comparison groups were determined. Children answered the items regarding their socio-demographic background, such as sex, ethnicity, age and date of birth, while parents answered questionnaires regarding parental education level and monthly household income.

### Impact evaluation

Impact evaluation included primary outcome measures, namely anthropometric measurements, knowledge, attitude and practice on nutrition, eating behaviours, physical activity; and secondary outcome measures included psychological distress, cognitive performance and health-related quality of life.

### Primary outcomes

#### Anthropometric measurements

Body weight of the children was measured using weighing scale and recorded to the nearest 0.1 kg. Height of the children was measured using stadiometer and recorded to the nearest 0.1 cm. Body weight and height were used for BMI calculation using the BMI formula BMI = weight (kg) / height^2^ (m^2^) [33]. The z-scores of weight-for-age (WAZ), height-for-age (HAZ) and BMI-for-age (BAZ) were computed using WHO AnthroPlus software [34], the nutritional status of children was obtained by comparing the z-scores against the WHO Growth Reference 2007 tables [33]. Waist circumference was measured by using Lufkin Executive diameter steel tape Model W606 PM. Abdominal obesity was determined by referring to the 90th percentile cut-off-point of waist circumference for children aged 7–11 years [3]. Percentage of body fat for children aged 10–11 years was measured using Omron HBF-306 Body Fat Analyzer Scale (Omron Corporation, Japan). Based on the obtained body fat percentage, the children were categorised into normal and high body fat percentage [35]. All assessments by qualified researchers followed the International Society for the Advancement of Kinanthropometry (ISAK) procedures.

#### Knowledge, attitude and practices on nutrition

Knowledge, attitude and practices on nutrition of children were measured by using the knowledge, attitude and practices on the modules of Healthy Kids Programme [30]. The questionnaire consisted 30 knowledge items in the format of multiple choices. Each knowledge on nutrition item had four answer options. Each correct response was allocated one point and an incorrect answer was allocated 0 point. The possible range of scores for knowledge was between 0 and 30. A higher score indicated a higher level of knowledge on nutrition. Besides, there were 30 attitude items. Each attitude item was measured on a 3-point Likert scale; from agree (3 points) to disagree (1 point). The possible range of scores for attitude was between 10 and 30. The total attitude score was summed up and a higher attitude score indicated better attitude on nutrition. In addition, there were a total of 30 practice items. The practice items were assessed on a 5 point-frequency scale, ranging from almost every day [5] to never [1]. The possible range of scores for practice was 10–50. All the frequency points were summed up, and a higher score indicated healthier practice on nutrition by the children.

#### Eating Behaviours

Eating behaviours of the children, which included main meal consumption and snacking behaviour were assessed based on the Eating Behaviours Questionnaire (EBQ) [36]. This questionnaire was designed to measure the frequency of main meal consumption (breakfast, lunch and dinner) and frequency of snacking between meals (morning tea break, evening tea break and supper). The frequency of meal consumption was based on number of days consumed in a week [36]. For snacking behaviour among the children, the number of days that the children consumed morning tea, afternoon tea and supper in a week were asked.

#### Physical activity

Physical Activity Questionnaire for Children (PAQ-C) is appropriate for elementary school-aged children (approximately ages 8–14 years) who are currently in the school system and have recess as a regular part of their school week [37, 38]. The PAQ-C is a self-administered, 7-day recall instrument, which provides a summary physical activity score derived from nine items, each scored on a 5-point scale. Item 1 (spare time activity) from no activity = 1; 7 times or more = 5. Items 2 to 8 (PE, recess, lunch, right after school, evening, weekends) from lowest activity response = 1 or highest activity response = 5. Item 9 (mean of all days of the week) from none = 1; very often = 5. Item 10 (identifies students who are unusual active during the previous week). By adding up all means of the first nine items in PAQ-C, a summative score of physical activity was obtained. A score of 1 indicated low physical activity level, whereas a score of 5 indicated high physical activity level. The Cronbach’s alpha of PAQ-C was 0.89 and it was higher than the acceptance level (0.60) [37].

### Secondary outcomes

#### Psychological distress

The Revised Child Anxiety and Depression Scale (RCADS-30) was used to measure symptoms of psychological distress, namely separation anxiety disorder, social phobia, generalised anxiety disorder, panic disorder, obsessive compulsive disorder, and major depressive disorder [39]. A 30-item version of RCADS (RCADS-30) was developed whereby this briefer version has five to six items per subscale. A self-report scale was used with subscale corresponding to separation anxiety disorder (5 items), social phobia (5 items), generalised anxiety disorder (5 items), panic disorder (5 items), obsessive compulsive disorder (5 items) and major depressive disorder (5 items). Items were scored 0–3 corresponding to never, sometimes, often and always respectively. A higher score indicated having more severe anxiety and depression symptoms [40]. The internal consistency of the RCADS-30 was tested and the Cronbach’s alpha for total scale was 0.89, with alpha coefficients for the separate RCADS-30 subscales ranging from 0.68 (obsessive-compulsive disorder) to 0.78 (generalised anxiety disorder) [40].

#### Cognitive performance

Raven’s Coloured Progressive Matrices (CPM) was used to assess cognitive performance of children [41]. This test contained 36 items with three sets of 12 items in each (sets A, AB and B) from the standard matrices. Most items were presented on a coloured background to make the test visually stimulating for participants. Each child needed around 15 min to complete the test. Children were asked to find and complete the missing pattern. Each correct answer was given 1 mark. The raw score on the coloured progressive matrices test ranged between 0 and 3. The child’s mental age is thus the age at which the median score is equal to his or her raw score. This score was converted into a standard score based on the Raven’s CPM norm table. A higher score indicated better cognitive performance.

#### Health-related quality of life

Pediatric Quality of Life Inventory 4.0 (PedsQL 4.0) was used to assess health-related quality of life (HRQoL) among children aged 8–12 years [42]. There was a total of 23 items from 4 subscales for child report: My health and activities; My feelings, I can get along with others and About school. Children were asked to recall health-related problems in the past 1 month and rate each item on a five-point Likert scale (0 = never, 1 = almost never, 2 = sometimes, 3 = often, 4 = almost always). Scores of all items were plotted on a 0-100 point scale (0 = 100, 1 = 75, 2 = 50, 3 = 25, 4 = 0). Higher total PedsQL scores corresponded to better HRQoL. The Cronbach’s alpha of PedsQL was 0.89 and it was higher than the acceptance level (0.60) [43].

### Process evaluation

Process evaluation of the SNP consisted of evaluation of attendance rate and programme feedback among the intervention groups. The attendance rate was assessed by using the attendance list for implementation of School Nutrition Campaigns 1, 2 and 3, respectively. Teachers needed to use the attendance list prepared by the researchers and took the attendance of children for each camp. Overall attendance rate and attendance by each camp were calculated. Programme feedback forms for three camps were self-administered by children after completing each of the campaigns. Percentage of programme feedback forms submitted by each camp was calculated. The attendance rate and programme feedback of TOT for teachers and TOT for canteen food handlers were also assessed in this study.

### Data analysis

The evaluation of the study was based on the modified intention-to-treat analysis to retain children in the study [44]. Children who fulfilled the following criteria would be included in the data analysis process:
i.Children of the intervention group who have attended at least two camps in the School Nutrition Programmeii.Children from both the intervention and comparison groups who had completed Pre-Intervention, Post-Intervention I and Post-Intervention II.

All statistical analysis will be conducted using IBM SPSS statistics 24.0. Descriptive analysis such as frequency and percentages, will be reported for categorical variables, while means and 95% confident interval will be reported for continuous variables. Skewness test of normality will be used to assess the normality of continuous variables. A value of skewness within the range of ±2.0 will be considered as normally distributed [45]. The Chi-square Test or Fisher’s Exact Test will be used to determine the association between two or more groups of categorical variables. The Independent sample t-test will be used to compare the mean values of the continuous variables between intervention and comparison groups and Paired sample t-test will be used to compare the mean values at pre-intervention and post-intervention within the intervention and comparison groups.

Simple linear mixed model will be conducted to determine the association of each covariate (such as time, group, child’s age, parental education level and school type) with all the dependent variables (namely knowledge, attitude and practice on nutrition, eating behaviour, physical activity, anthropometric measurement, psychological distress, cognitive performance and health-related quality of life). Multiple linear mixed model will be conducted to investigate the dependent variables between groups (intervention and comparison) over time, adjusted for covariates. Interaction term of time and group will be included in the model. The differences in all continuous variables between intervention and comparison groups will be determined at three time points (Pre-Intervention, Post-Intervention I and Post-Intervention II). The statistical significance will be set at *p* < 0.05. The data will be stored for future use after the completion of the study.

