## Methods/design

### Study design

The present study design was a quasi-experimental design. Out of 147 National Primary Schools in Batu Pahat district, a total of 143 National Schools met the inclusion criteria of being co-educational, non-religious, non-special educational, multi-ethnic and government funded schools. Then, these 143 schools were stratified based on the three main school types, namely i) National Primary School (SK), ii) National Chinese Primary School (SJKC) and iii) National Tamil Primary School (SJKT). Two schools from each stratified group were selected. One school was selected as Intervention Group (IG) and one as Comparison Group (CG) from each school type. All children from these selected schools were invited to participate in the study.

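### The modified intention-to-treat set is a per-protocol completer set: it filters only the intervention arm on camp attendance and drops any child with a missed assessment

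*Protocol article*

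**What the plan says.** In the protocol article, Data analysis opens with a label and a purpose: "The evaluation of the study was based on the modified intention-to-treat analysis to retain children in the study". It then makes entry conditional: "Children who fulfilled the following criteria would be included in the data analysis process". Two criteria follow:

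- Criterion i: "Children of the intervention group who have attended at least two camps".
- Criterion ii: "Children from both the intervention and comparison groups who had completed Pre-Intervention, Post-Intervention I and Post-Intervention II".

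No other analysis set is described, so this one serves every primary and secondary outcome.

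Three other places bear on the point:

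- The camps are the School Nutrition Campaigns, delivered in one arm only. The description of the intervention says "The children of the intervention group participated in three School Nutrition Campaigns, in addition to the standard Physical dan Health Curriculum", and of the other arm, "The children in the comparison group received standard Physical and Health Curriculum".
- Allocation is by school (Study design): "One school was selected as Intervention Group (IG) and one as Comparison Group (CG) from each school type".
- The main model (Data analysis) is longitudinal: "Multiple linear mixed model will be conducted to investigate the dependent variables between groups (intervention and comparison) over time, adjusted for covariates". It includes a time-by-group interaction. Independent-sample t-tests between the groups are planned as well.

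**The concern.** Criterion i selects children on something that happens after allocation, and only in the arm that has camps. The comparison arm keeps the counterparts of the poor attenders; the intervention arm loses them. If attendance is related to outcome, the two analysed groups differ for a reason other than the programme.

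Criterion ii applies to both arms but is a complete-case rule. A child seen at Pre-Intervention and Post-Intervention I is lost from that comparison for missing Post-Intervention II, although a linear mixed model can use the two visits.

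The aim of the study is the effectiveness of a school programme, and imperfect attendance is part of effectiveness. The programme also has a second component, the healthy canteen menu, which the article does not tie to camp attendance. Children below two camps may therefore have received a good part of the programme and still be removed. Readers who see the modified intention-to-treat label would credit the estimate with a protection it does not have.

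**Working it through.** **1. Who is admitted.** The criteria are listed without a joining word. On the natural reading, an intervention child must meet both i and ii, and a comparison child only ii. If either criterion were enough, an intervention child could still enter by a route that a comparison child does not have. On both readings the entry rules differ between the arms.

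**2. The plan's own figures (Sample size calculation).** Inputs: 195 per group, 80% response, mean changes in waist circumference of 0.1 and 2.2 cm, 80% power, 5% significance.

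- 195 / 0.80 = 243.75, so 244 per group and 488 in total. This reproduces.
- No SD is given. Solving n = 2σ²(1.96 + 0.842)² / 2.1² for n = 195 gives σ ≈ 7.40 cm, a standardised difference of 2.1 / 7.40 ≈ 0.284. This is derived. The article states an effect size of 0.09, which does not agree with it. The value 0.284 serves below only as a yardstick.

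**3. Bias from criterion i with no programme effect.** Let p be the share of otherwise complete intervention children excluded for attendance, and delta the gap between attenders and the excluded. The full-arm mean is (1 − p) × attenders + p × excluded, so the retained mean minus the full-arm mean is p × delta.

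- *Between-group t-test at a single visit:* delta is the gap in level at that visit.
- *Time-by-group interaction:* the bias is p × (gap at follow-up − gap at baseline). With p = 0.30 and a stable gap of 0.5 SD, the t-test is biased by 0.15 SD and the interaction by 0.30 × (0.5 − 0.5) = 0.

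Illustration with an assumed gap in change from baseline (the article gives neither p nor the gap):

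| p | gap in change (SD) | bias (SD) | share of 0.284 |
|---|---|---|---|
| 0.10 | 0.3 | 0.03 | 11% |
| 0.10 | 0.5 | 0.05 | 18% |
| 0.30 | 0.3 | 0.09 | 32% |
| 0.30 | 0.5 | 0.15 | 53% |

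**4. A second selection model.** Let q be the share excluded and rho the correlation between attendance propensity and favourable outcome change. The bias in SD is rho × φ(c) / (1 − q), where c is the q-quantile of the standard normal distribution. Assumptions: SD 7.40 cm, 195 per arm, no true effect, clustering by school ignored.

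| q | rho | bias (cm) | type I error |
|---|---|---|---|
| 10% | 0.1 | 0.14 | 5.4% |
| 10% | 0.3 | 0.43 | 8.9% |
| 10% | 0.5 | 0.72 | 16.1% |
| 20% | 0.3 | 0.78 | 17.9% |
| any | 0 | 0 | 5.0% |
| 10% | −0.3 | −0.43 | 8.9% |

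A positive sign favours the programme. The direction follows the sign of rho.

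**5. If the programme works.** Assume that children below two camps gain nothing and attenders gain 2.1 cm. The as-assigned effect is 2.1 × 0.90 = 1.89 cm at 10% exclusion and 2.1 × 0.80 = 1.68 cm at 20%. The filtered set would still report about 2.1 cm.

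**6. Loss of numbers.** If missed visits use up the 20% allowance, 244 × 0.80 ≈ 195 remain per arm. A further 10% lost to criterion i leaves about 176 intervention children, and power falls from 80.0% to 77.9%. The cost in precision is minor; the issue is selection.

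**The case against.** The strongest objections concern direction and size.

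- *Direction.* A reader might infer that the rule must favour the programme, so that a useless programme would look effective. The article does not support that. It reports no attendance data, zero correlation gives no bias, and a negative one reverses it. For anthropometry the less favourable direction is itself unclear, because the programme addresses both undernutrition and overnutrition. This objection stands: the bias is plausible in that direction, not established.
- *Size.* A reader might take 11% to 53% as the bias in the adjusted model. It is not, if the gap reflects habits already present at baseline, because a stable gap cancels in the time-by-group interaction. It does not cancel in the between-group t-tests at a single visit. In addition, p counts only children with all three assessments, since criterion ii already removes the others from both arms. This stands too.
- *Label.* Modified intention-to-treat has no single definition, the article cites a source for it that is not at hand, and the criteria are disclosed openly. A charge that the term is wrong by definition would go too far. What remains is the conflict within the section: a set meant to keep children in is defined by rules that take them out.
- *Design.* The study is quasi-experimental, so there is no stated randomisation for an intention-to-treat set to preserve. That is true, but a filter on one arm adds a further source of non-comparability to a comparison of three schools with three.

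Nor is this a matter left to a fuller analysis plan: the article states the rule explicitly.

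**Conclusion.** The point holds as a fault in what is written. The only analysis set in the article is a per-protocol completer set. It has a post-allocation attendance filter in one arm and a complete-case rule in both, at odds with its stated purpose and with a model that can use partial records. These facts rest on the text alone.

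The effect on the results is conditional. The estimate can be biased, plausibly but not certainly towards the programme, and the amount cannot be fixed from the article. The illustrative range is 0.03 to 0.15 SD, for an assumed 10% to 30% excluded and an assumed gap in change of 0.3 to 0.5 SD, set against a back-solved 0.28 SD. Under a gap that is stable from baseline, the interaction carries no bias and only the single-visit comparisons do. Because the rule governs every effectiveness estimate, it should be changed before the analysis.

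**What to change.** - **Main analysis.** Include all enrolled children of the six schools, in the group of their school, regardless of camps attended. Enter every available assessment in the likelihood-based linear mixed model, with no requirement to have completed all three.
- **Sensitivity analysis.** Keep the set with at least two camps and all three assessments, label it per-protocol, and do not call it modified intention-to-treat.
- **Reporting.** Give the number of children removed by each criterion in each arm, and compare the baseline values of removed and retained children. That replaces the assumed p with an observed one.

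The data should exist: the Measurements section says that all participants in both groups were assessed at the three time points, and Process evaluation says that attendance was taken at each camp. The assessments of poor attenders must be kept. The cost is a change of wording and slightly more analysis work. The estimated effect may shrink, and the use of partial records assumes that visits are missing at random given the observed data.

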**Methods/design:**

This quasi-experimental study aimed to evaluate the effectiveness of the SNP between intervention and comparison groups before and after the SNP, and after a 3-month follow-up. The SNP consisted of two main components, whereby three nutrition education sessions were implemented by trained teachers using three standardised modules, and healthy school food environment was implemented by the canteen food handlers with the provision of healthy menu to children during school recess times. Children from intervention group participated in the SNP, in addition to the standard Physical and Health Curriculum. The comparison group attended only the standardised Physical and Health Curriculum and the school canteen food handlers were reminded to follow the standard canteen guidelines from the Ministry of Education Malaysia. The assessment parameters in evaluating the effectiveness of the programme were knowledge, attitude and practice on nutrition, eating behaviours, physical activity, body composition, psychological distress, cognitive performance and health-related quality of life. Assessments were conducted at three time points: pre-intervention, post-intervention and 3-month follow-up.

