### Participants

This study was conducted in six selected schools in Batu Pahat District, Johor State, Malaysia. School authorities (principal and teachers) and canteen food handlers from three selected intervention schools were invited to participate in the study. All Malaysian children (males and females) who were enrolled in Standards 1 to 5 (aged 7 to 11 years) and who was either Malay, Chinese or Indian were invited in the study (Fig. 1). Upon request from the Ministry of Education (MOE) Malaysia, children in Standard 6, who would be attending the National Primary School Evaluation Test, were excluded from the study. In addition, children with learning disorders, obvious genetic disorders such as attention deficit hyperactivity disorder (ADHD) were excluded from the study. The children were assessed prior to the start of the programme (Pre-Intervention), one-week right after completing SNP (Post-Intervention I) and three-month follow-up without intervention (Post-Intervention II).

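### Whole schools form the groups, but the planned t-tests, chi-square tests and paired tests treat children as independent, and no effect for school is stated for the mixed model

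*Protocol article*

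**What the plan says.** All references are to the protocol article.

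- **Study design.** The study is declared quasi-experimental: "The present study design was a quasi-experimental design". Schools were stratified into three types. Then "Two schools from each stratified group were selected", and "One school was selected as Intervention Group (IG) and one as Comparison Group (CG) from each school type". The Participants section confirms the count: "This study was conducted in six selected schools in Batu Pahat District, Johor State, Malaysia".
- **Delivery.** Both components reach children through their school. Trained teachers run the education sessions, and the "healthy school food environment was implemented by the canteen food handlers with the provision of healthy menu to children during school recess times".
- **Data analysis, simple tests.** For continuous variables, "The Independent sample t-test will be used to compare the mean values of the continuous variables between intervention and comparison groups". Paired t-tests compare pre- with post-intervention means within each group. For categorical variables, "The Chi-square Test or Fisher’s Exact Test will be used to determine the association between two or more groups of categorical variables". Significance is set at p < 0.05, and no test is marked as descriptive.
- **Data analysis, mixed model.** "Multiple linear mixed model will be conducted to investigate the dependent variables between groups (intervention and comparison) over time, adjusted for covariates". A time-by-group interaction is included. The covariates are given as examples: time, group, age, parental education and school type. School is not named, and no random effect is described.
- **Sample size calculation.** 195 children per group, raised to 244 for an 80% response rate, 488 in total. Neither an ICC nor a design effect appears.

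**The concern.** A t-test or chi-square test on individual children assumes that their outcomes are independent. Children in one school share teachers, canteen, menu and local events, and here all of them are in the same group. The comparison is in effect three schools against three. If outcomes vary between schools for reasons other than the programme, a child-level test counts that variation as if it had been averaged over nearly 400 independent children.

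School type does not repair this. It is the stratum. Within each type there is one school per group, so the difference between the two schools is fully confounded with group, and fitting school type leaves that difference where it was.

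The group-by-time contrast fares better than a comparison at a single visit, because stable differences between schools cancel from it. School-specific changes over time do not cancel. An independent-sample t-test at one visit has neither protection: it also carries any baseline difference between non-randomised groups.

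The paired tests raise a separate problem. Children grow, so a change within a group is expected with or without the programme.

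At stake is whether p < 0.05 carries its stated meaning for the outcomes tested this way.

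**Working it through.** **Inputs from the document.** Six schools, three per group; 195 per group before and 244 after the response adjustment; waist change 0.1 cm (intervention) and 2.2 cm (comparison) in the source study; 80% power; 5% significance (two-sided assumed).

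**Assumed inputs.** Equal school sizes, so 195 / 3 = 65 responding children per school. ICC of change from 0.002 to 0.05; the document gives no value.

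**Step 1: the plan's own figures.** 195 / 0.8 = 243.75, so 244 per group and 488 in total. This reproduces. The 195 cannot be checked directly because no SD is given. Solving 195 = 2·SD²·(1.96 + 0.84)² / 2.1² gives SD = 7.40 cm, a standardised difference of 2.1 / 7.40 = 0.284. The step from 195 to 244 is fully explained by the response rate, so it contains no allowance for clustering.

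**Step 2: type I error of a child-level test.** Design effect DE = 1 + (65 − 1)·ICC. True error of a nominal 5% test = 2·[1 − Φ(1.96 / √DE)].

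| ICC of change | DE | True type I error | Effective n per group (195 / DE) |
|---|---|---|---|
| 0.002 | 1.128 | 6.5% | 173 |
| 0.005 | 1.32 | 8.8% | 148 |
| 0.01 | 1.64 | 12.6% | 119 |
| 0.03 | 2.92 | 25.1% | 67 |
| 0.05 | 4.20 | 33.9% | 46 |

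**Step 3: does school type help?** Simulation with no programme effect, 3 types × 2 schools × 65 children, 4,000 runs per ICC. Rejection rates:

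| ICC | t-test | School type also fitted |
|---|---|---|
| 0 | 4.6% | 4.7% |
| 0.01 | 13.5% | 13.5% |
| 0.05 | 34.2% | 34.7% |

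Fitting school type makes no material difference.

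**Step 4: the paired tests.** If the implied SD of 7.40 cm applies to change, 195 comparison children with a mean change of 2.2 cm give t = 2.2 / (7.40 / √195) ≈ 4.2. A group without the programme would show a clearly significant change.

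**Step 5: analyses that respect school.** A school-level analysis (mean change per school, intervention minus comparison within type, t on 2 df) held its error at about 5% in simulation. A simplified mixed model on change scores (school random, type fixed, Satterthwaite df; 200,000 runs) had an error of 5.8% at ICC 0.01 and about 7% at 0.03 to 0.05. At ICC 0.01 it estimated the school variance as zero in about 45% of runs and then reverted to child-level degrees of freedom.

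**Step 6: power on 2 df.** With a 2.1 cm difference and SD 7.40 cm, the noncentrality is 2.1 / (7.40·√(2·DE / 195)), which is 2.19 at ICC 0.01 and 1.37 at ICC 0.05. The noncentral t on 2 df gives power of about 25% and 13%, against the planned 80%.

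**The case against.** **The mixed model may already contain a school effect.** The covariates are introduced as examples, the random structure is not described, and a condensed article can leave this to a fuller analysis plan. This stands. A reader might infer that the model omits school; the document does not show that, only that no effect for school is stated. The objection does not reach the t-tests, paired tests and chi-square tests, which are written out as planned analyses.

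**The simple tests are not labelled as tests of effectiveness.** Partly right. The chi-square sentence names no outcome or visit, and the adjusted model with the time-by-group term looks like the main analysis. But the t-test sentence compares the two groups, the paired sentence is explicitly pre versus post, and one significance threshold is set for everything.

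**Differences between schools need not become programme effects.** A reader might infer that any difference among the six schools would be reported as an effect of the programme. That goes too far: stable differences cancel from the group-by-time contrast, and the size of what remains depends on an ICC that the document does not give. At 0.002 the inflation is slight.

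**Accounting for school does not make the groups comparable.** Correct. It corrects the stated uncertainty. It cannot separate the programme from whatever else differs between non-randomly selected schools.

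**Conclusion.** The point holds for the tests that the plan spells out. Groups made of whole schools are to be compared with child-level tests at p < 0.05, and the one school-related covariate named cannot stand in for school. For the mixed model, the accurate statement is that its handling of school is not stated.

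On the assumptions of 65 children per school and an ICC of change between 0.002 and 0.05, the true error of a nominal 5% child-level test runs from about 6.5% to 34%; it passes 10% by an ICC of 0.01. These figures illustrate a range and do not estimate this study's error rate. The paired tests cannot show effectiveness at any ICC, since the plan's own source figures give a change of 2.2 cm in the comparison group.

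**What to change.** In the Data analysis section:

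1. Name the group-by-time contrast as the test of effectiveness.
2. State that it accounts for school, by one of two routes. The first is a school-level analysis: mean change per school, intervention minus comparison within school type, t on 2 df. The second is a mixed model with random effects for child, school and school-by-time and small-sample degrees of freedom, checked against the school-level analysis because six schools may give a school variance of zero.
3. Analyse categorical outcomes by school-level proportions or by a model that accounts for school.
4. Label the child-level t-tests, paired tests and chi-square or Fisher tests as descriptive.

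This needs new analysis wording and no new data. The cost in precision should be disclosed: intervals widen, and on 2 df power is about 25% at ICC 0.01 and 13% at ICC 0.05 with the implied SD. The report should also say that confounding from non-random school selection remains.
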